## Abstract

**Background:**

Results from previous studies suggest that bodily movements, spanning from gestures to whole-body movements, integrated into academic lessons may benefit academic learning. However, only few studies have investigated the effects of movement integrated into reading practice. The PLAYMORE study aims to investigate the effects of two interventions focusing on a close and meaningful coupling between bodily movement and academic content on early pre-reading and word recognition skills in children. Further, the study aims to compare two interventions involving either hand movements (i.e. using arms and hands) or whole-body movements (i.e. using the whole body). Potential mediating factors underlying the link between bodily movement on early pre-reading and word recognition skills will be explored.

**Methods/design:**

The PLAYMORE study will be conducted as a three-armed randomized controlled trial including children aged five to six years recruited from four schools in the Copenhagen area, Denmark. Stratified by class, children will be randomly allocated to one of three 8-week intervention/control periods: 1) teaching involving whole-body movements, 2) teaching involving hand movements (i.e. arms and hands) or 3) teaching involving minimal motor movements (i.e. seated on a chair using paper and pencil). Outcome measurements, including pre-reading and word recognition skills, will be collected before and after the intervention period to assess the intervention effects. This study protocol follows the SPIRIT guidelines.

**Discussion:**

The PLAYMORE study will add to the current knowledge concerning the link between bodily movement and academic performance with important details about pre-reading and word recognition skills in preschool children. If effective, evaluation of the implementation of the PLAYMORE program should be conducted in order to investigate whether the effects can be transferred into standard school settings. The PLAYMORE study will lay the foundation for future research that have the potential to inform the political and scientific debate and importantly, to provide teachers with detailed information of how to implement movements effectively during teaching in order to support and motivate children in the process of learning to read.

**Trial registration:**

The study was retrospectively registered in ClinicalTrials.gov (NCT04618822) the 5th of November 2020.

## Background

The acquisition and development of competent reading skills in childhood are critical to functioning and well-being later in life. Poor spelling and reading skills in children and adolescents have been associated with poor academic achievement [67, 74, 89], school dropout [20, 55], and lower occupational status in adulthood [62, 74]. Initially, when learning to read, the acquisition of phoneme awareness and letter knowledge is of great importance. Letter knowledge is required in order to understand the alphabetic code, that is, the fact that sounds and letters can combine, which, in turn, will allow for the development of basic word reading accuracy. Accordingly, phoneme awareness and letter knowledge measured before the outset of formal reading instruction are unique predictors of later reading and spelling abilities [11, 29, 36, 48, 56, 68]. Given the fundamental role of reading abilities in modern society, it is essential to identify forms of instruction and practice that support and motivate children in the process of learning to read with a specific focus on the acquisition of phoneme awareness, letter knowledge and decoding abilities in the first school year.

School-based interventions involving bodily movement (spanning from less pronounced movements such as e.g. gestures to physical activity (PA) in terms of e.g. exercise) have been recognized as a potential strategy to support academic learning in children and adolescents and several reviews in this field have been published (e.g. [3, 18, 22, 23, 51, 58–60, 71, 87]). In general, the effects on overall academic performance are found to be small, also when summarizing isolated effects within subdomains such as reading and mathematics [3, 22, 23, 51, 71]. However, bodily movement is a multifaceted construct and the mechanisms through which cognition and learning are effected depend highly on the characteristics of the movement activities (e.g. type, movement range) [5, 19, 53]. Thus, when investigating the link between bodily movement and academic performance, it is important to differentiate between different types of movement activities. During the last decade, much research has focused on the relationship between general PA, in terms of e.g. physical exercise, cognitive performance and academic learning (for reviews see e.g. [24, 71]). From laboratory-based and strictly controlled studies, it is evident that cognitive performance, in particular executive functions (which play an important role in the development of e.g. word recognition and spelling skills [12, 39, 80]) can be enhanced following a single bout of PA ([15, 34, 44], for review see [14, 35]). Moreover, though equivocal, results from some experimental studies suggest that several bouts may benefit executive functions in children and adolescents [21, 33, 79]. Physiological mechanisms underlying the acute effects of PA on cognition comprise transient increase in peripheral levels of catecholamines [16, 72], steroid hormones [8, 32] and growth factors [28, 72] as well as changes in cerebral oxygenation and cerebral blood flow [25]. In addition, increased catecholamines and growth factor levels induced by several bouts of PA can eventually lead to e.g. structural brain alterations (i.e. new vascular and neural structure) affecting cognitive performance (for review see [81]). However, whether this effect transforms into improved academic learning, when PA is conducted in a school setting, is still unclear, since high quality school-based intervention studies are limited and often conducted as multi-component studies including PA as one of more intervention components.

Another promising, but less investigated, approach is the coupling of movement and academic content during academic lessons. This approach rely on principles drawn from theories of embodied cognition and is often referred to as *embodied learning* [49, 73]. Briefly, embodied cognition suggests that human cognition develop from the body’s interactions with the surrounding environment [70]. Interestingly, it has been demonstrated that both visual and motor brain networks are activated during cognitive tasks such as reading and problem-solving, suggesting that task performance not only rely on e.g. visual information but also sensory information gained through bodily experiences (discussed by e.g. [90]). As such, actions involving task relevant information may support learning of the specific task in addition to just hearing or observing it (i.e. the enactment effect) [26]. Based on this view, embodied learning activities aim to create a close coupling between the movement and the specific task to be acquired, but vary in regards to e.g. the level of bodily engagement, task integration [73] and congruency between the movement and the task at hand [40]. Over the years, a large body of research has emerged mainly using gestures or hand movements but also whole-body movements during learning (e.g. [2, 5, 19, 53, 66]). For example, Mavilidi and colleagues used gestures and physical exercise during teaching of 3–5 year-old children learning a new language over a 4-week period and evaluated the effects on new words learned [53]. Using a four-armed randomized controlled design, they found that gestures as well as physical exercise, particularly when movements were integrated into the learning task, had beneficial effects on learning. A recent systematic review (*unpublished, in review*) summarized studies investigating the effects of bodily movement on early first language word recognition and spelling skills in children and found that only few studies of limited quality focused on interventions founded in the embodied learning theory, i.e. involving activities with a close coupling between the movement and the academic task. The identified studies mainly focused on handwriting [17, 46, 61, 69, 84, 85], copying or tracing letters/words [6, 37, 46, 50, 85, 91] and only four studies included whole-body movements (i.e. embodying letters, walking the outline of letter) [4, 7, 19, 52]. Considering the limited amount of studies involving whole-body movements in combinations with the large variety of movement components included in these studies, it is still uncertain whether such activities have a larger impact on word recognition and spelling skills compared to teaching methods not incorporating motor activities. Such information is needed in order to enable a construction of general guidelines and specific instructions for integrating PA in a meaningful way into the school day.

Consequently, the current study aims to investigate the effects of two interventions focusing on movement activities with a close and meaningful coupling between the movement and the academic content on pre-reading and word recognition skills in children. Previous studies focusing on mathematics [5] or second language [53] suggest that the effects may depend on the motor modality used (i.e. whole-body or hand movements). Thus, another aim of the study is to compare the two interventions involving either hand movements (i.e. using arms and hands) or whole-body movements (i.e. using the whole-body). Lastly, to explore potential mediating factors underlying this relationship, the intervention effects on intrinsic motivation and cognitive performance will be evaluated. The study will be conducted as a three-armed randomized controlled trial designed to test superiority of two interventions as compared with a control. Included subjects will be randomly allocated in an approximate 1:1:2 fashion to either 1) teaching involving whole-body movements, 2) teaching involving hand movements or 3) teaching involving minimal motor movements (i.e. seated on a chair using paper and pencil).

It is hypothesized that the two interventions involving hand or whole-body movements, respectively, will induce a larger effect on pre-reading and word recognition skills compared to a teaching method where movement is reduced to a minimum (i.e. seated using paper and pencil). In addition, based on current literature within mathematics [5], it is expected that the intervention involving whole-body movements induces the largest effects compared to the intervention involving hand movements.

## Methods/design

The study was retrospectively registered in ClinicalTrials.gov (NCT04618822) the 5th of November 2020. This study protocol (1st version, October 2020) follows the SPIRIT guidelines [13].

### Study design

The study will be conducted as a three-armed randomized controlled trial including two intervention groups and one control group (CG) (Fig. 1, study design and flow of participants). Intervention activities will be completed as either whole-body movements (WM, intervention group I) or hand movements (HM, intervention group II) over an 8-week period at four primary schools. Using random selection of sealed envelopes, participants will be randomized stratified by class in an approximate 1:1:2 fashion to either WM, HM or CG. Specifically, within each class six subjects will be assigned to WM, six subjects to HM, while the remaining subjects will constitute the CG. The project leader will be responsible for all steps related to the enrollment and allocation of participants. Outcome measurements will be collected before and after the intervention period enabling assessment of the intervention effects. A schematic diagram of time schedule of enrolment, interventions and assessments are presented in Table 1.

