### Justification of sample size

The study has not been formally powered based on results from a specific study, as no equivalent study with similar outcomes exists. In general, the effects of physical activity lessons are observed to be small to moderate [60]. In addition, a study based on the embodied learning theory found small to moderate effect sizes in regards to letter knowledge when comparing learning activities involving whole-body movements with visual learning activities [4]. Given three groups with an equal number of participants in each group, power calculations suggest that 158 subjects are needed to achieve a power of 80% and a level of significance of 5% for detecting an effect size of 0.25 between groups. Since the control group will include approximately twice as many participants as each of the intervention groups, 212 subjects are needed to detect an effect size of 0.25 (intervention group: *n* = 53, control: *n* = 106). Accounting for a 20% dropout rate or data loss for other reasons, 265 participants will be included in the study. Power calculations have been done using Gpower [27].

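### The single 80% power figure is an omnibus figure; it does not describe the whole-body versus hand comparison, which stays at 53 v 53

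*Protocol article*

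**What the plan says.** Under Study design, children are randomised within class, approximately 1:1:2: "within each class six subjects will be assigned to WM, six subjects to HM, while the remaining subjects will constitute the CG".

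The last part of the Background gives pairwise hypotheses. Each movement arm is expected to beat the control. Comparing the two movement arms is a further aim, with a direction: "it is expected that the intervention involving whole-body movements induces the largest effects compared to the intervention involving hand movements".

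Justification of sample size makes one calculation, at 80% power and 5% significance. It starts from "Given three groups with an equal number of participants in each group", arrives at 158 children, and describes the target as "for detecting an effect size of 0.25 between groups". The metric of 0.25 is not named. Because CG will be about twice the size of an intervention arm, the text then says that "212 subjects are needed to detect an effect size of 0.25", made up of 53, 53 and 106. Finally: "Accounting for a 20% dropout rate or data loss for other reasons, 265 participants will be included in the study". No power is given for any single pair of arms.

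**The concern.** A reader will take an 80% figure described as being between groups to cover the comparisons that the trial sets out to make. An omnibus test asks only whether the three means differ somewhere. It can have 80% power or more while one of the pairs has much less.

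WM versus HM is the pair most exposed, because the step from 158 to 212 adds nobody to either movement arm. If that comparison comes out null and is read against the 80% statement, it may be taken as evidence that the type of movement makes no difference. The Discussion notes that hand movements may be easier for teachers to implement, so that reading could influence practice.

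**Working it through.** **Inputs.** From Justification of sample size: 5% significance, 80% power, effect size 0.25, N = 158 in three equal groups, 212 = 53 + 53 + 106, 20% loss, 265 enrolled. From the Background: expected order WM ≥ HM ≥ CG. Assumed here: two-sided pairwise tests, outcome SD of 1, no allowance for clustering.

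**1. Reproducing the plan's figures.** For a three-group F test with Cohen's f, the noncentrality is λ = N·f².

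- N = 157: power 79.95%.
- N = 158: λ = 158 × 0.0625 = 9.875, power 80.2%. This is the smallest N that reaches 80%.
- 212 = 4 × 53. The equal-group size of about 53 is kept in each movement arm and CG is doubled. With f held at 0.25, omnibus power at 212 is about 91%.
- 212 / 0.80 = 265.

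The arithmetic is sound once 0.25 is read as f and 80% as omnibus power.

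**2. Precision of each contrast at 53/53/106.** The variance factor is 1/n₁ + 1/n₂.

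- Each control contrast: 1/53 + 1/106 = 0.0283.
- WM versus HM: 1/53 + 1/53 = 0.0377.

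**3. Difference detectable with 80% power.** This is (1.960 + 0.842) × √(variance factor).

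- WM versus HM: 2.802 × √0.0377 = 0.544 SD (0.549 by the t test).
- Each control contrast: 2.802 × √0.0283 = 0.471 SD (0.474 by the t test).

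**4. What f = 0.25 implies for WM–HM.** Write a = WM − HM and b = HM − CG. With equal-group weights, f² = (2/9)(a² + ab + b²). The expected order means a ≥ 0 and b ≥ 0, so for fixed f the largest a occurs at b = 0.

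| Reading of 0.25 | WM–HM difference (SD) | Power, 53 v 53 (t test) |
|---|---|---|
| f, HM = CG (b = 0): a = 0.25 × 3/√2 | 0.530 | 77% (78% by z) |
| f, equally spaced (a = b): a = 0.25 × √1.5 | 0.306 | 35% |
| Standardised difference of 0.25 | 0.25 | 25% |

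On the last reading, each control contrast (53 v 106) has about 31% power.

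**5. When WM–HM would exceed 80%.**

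- f weighted 1:1:2 with HM = CG: f² = (1/4)(3/4)a², so a = 0.25/√0.1875 = 0.577 and power is about 84%.
- CG midway between WM and HM: a = 0.25 × √6 = 0.612 and power is about 88%.
- A one-sided test: about 82% at 0.5 SD.
- No dropout: 265/4 ≈ 66 per arm, about 82% at 0.5 SD.
- Credit for baseline adjustment: a baseline–outcome correlation r shrinks the detectable difference to 0.549 × √(1 − r²). Bringing it to 0.530 takes r of about 0.26; bringing it to 0.306 takes about 0.83.

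The sample-size section states none of these.

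**The case against.** The strongest reply is that the protocol never claims 80% for each pair, and that its calculation is correct for the test it appears to use. The Background describes the trial as designed for superiority over control, with WM versus HM as a further aim. Doubling CG takes nothing from WM versus HM relative to the 158-child calculation, since that pair is 53 v 53 either way. In the most favourable case under the expected order the shortfall is only two or three points, and a modest baseline correlation would close it. All of this stands, and it limits the point to how power is stated.

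A reader might go further in three ways that the documents do not support.

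- **That the 1:1:2 split is wasteful and should be replaced by equal arms.** At a fixed total of 212 the control contrasts do have the same variance as under equal arms (2/70.67 = 0.0283). But charging the split with 54 extra children (212 − 158) fixes the movement arms at 53 instead, which is a different comparison; there the added controls do improve the control contrasts. The protocol claims no efficiency gain. Table 1 and the materials in Table 3 are built for groups of six, and the Conclusion leaves larger groups to later work.
- **That WM–HM power is one fixed number,** such as the 72% obtained at 0.5 SD. It depends on the pattern of means, so only a range or a detectable difference is defensible.
- **That the sample size is miscalculated.** It reproduces.

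**Conclusion.** The point holds as a misdescription of power, not as an arithmetic error or a faulty allocation. The single 80% figure belongs to an omnibus F test with f = 0.25 and does not describe the pairwise hypotheses. For WM versus HM, 80% power needs about 0.55 SD, against about 0.47 SD for each control contrast. With equal-group f = 0.25 and WM ≥ HM ≥ CG, WM–HM power is at most about 77–78%, and that maximum requires HM to equal CG, contrary to the hypothesis that HM beats control. Equal spacing, which fits both hypotheses, gives about 35%.

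These figures assume 212 analysed children, two-sided 5% tests and no clustering. They do not depend on any intraclass correlation, because the document gives none.

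**What to change.** Keep six children per movement group and the planned total. In Justification of sample size:

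1. State that 0.25 is Cohen's f and that 80% at N = 158 is the power of the three-group omnibus test.
2. Replace the single statement with figures by contrast: with 53/53/106 analysed, two-sided 5% and before clustering, the difference detectable with 80% power is about 0.55 SD for WM versus HM and about 0.47 SD for each movement arm versus CG.
3. State that WM versus HM is not powered at 80% for the planned effect, so a null result there is inconclusive and not evidence that the two forms of movement are equivalent.
4. If credit is to be taken for baseline adjustment or a one-sided test, state the assumption and recompute from it.

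The cost is a few sentences. Recruitment, allocation, materials and staffing do not change.

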**Fig. 1 Fig1:**
[figure not shown]
Study design and flow of participants

**Table 1 Tab1:** Schedule of enrolment, interventions and assessments in the PLAYMORE study

		STUDY PERIOD											
Activity or assessment	School/class /group /individual level	Recruite-ment	Baseline	Intervention period (8 weeks)								Post	3-month follow-up
				1	2	3	4	5	6	7	8		
Contact to schools	School	**●**											
Eligibility screen	Individual	**●**											
Consent (parents)	Individual	**●**											
Inclusion	Individual	**●**											
Randomization	Individual		**●**										
**INTERVENTIONS/CONTROL** (3*30 minutes/week)													
Whole-body movements	Group (6 subjects)			**●●●**	**●●●**	**●●●**	**●●●**	**●●●**	**●●●**	**●●●**	**●●●**		
Part-body movements	Group (6 subjects)			**●●●**	**●●●**	**●●●**	**●●●**	**●●●**	**●●●**	**●●●**	**●●●**		
Control	Group (app. 12 subjects)			**●●●**	**●●●**	**●●●**	**●●●**	**●●●**	**●●●**	**●●●**	**●●●**		
**ASESSMENTS**													
***Reading skills***													
Word reading with pictures	Individual		**●**									**●**	**●**
Word reading without pictures	Individual		**●**									**●**	**●**
Naming of letter sounds	Individual		**●**									**●**	**●**
Letter Fluency	Individual		**●**									**●**	**●**
Letter test 2	½ class		**●**									**●**	**●**
Word reading test 1	½ class		**●**									**●**	**●**
Knowledge of trained letter- sound correspondences	½ class		**●**									**●**	**●**
***Cognitive performance***													
Digit Span	Individual		**●**									**●**	**●**
N-back	Individual		**●**									**●**	**●**
***Motor skills***													
Flamingo Balance test	½ class		**●**									**●**	**●**
9-hole pegboard	Individual		**●**									**●**	**●**
***Compliance data***													
Presence	Individual			**●●●**	**●●●**	**●●●**	**●●●**	**●●●**	**●●●**	**●●●**	**●●●**		
Active participation	Individual			**●●●**	**●●●**	**●●●**	**●●●**	**●●●**	**●●●**	**●●●**	**●●●**		
Session completion	Group			**●●●**	**●●●**	**●●●**	**●●●**	**●●●**	**●●●**	**●●●**	**●●●**		
Compliance to protocol	Group			**●●●**	**●●●**	**●●●**	**●●●**	**●●●**	**●●●**	**●●●**	**●●●**		
***Intrinsic motivation***	Individual				**●**		**●**		**●**		**●**		

Adapted from the SPIRIT guideline (Chan et al., 2013)

### Participants and recruitment

The intervention is targeted children five to six years old who have just started school. In Denmark, children start school in August of the calendar year in which they turn six. However, formal reading instruction is not a part of the first school year (referred to as “*Grade 0*”) which has been compulsory in Denmark since 2009 but remains a preparation year [78]. Thus, teachers are required to prepare students for formal reading instruction in later grades and letter knowledge is emphasized as an area meriting special attention [78]. The intervention period will start approximately 1.5 months after children have started Grade 0. At the beginning of Grade 0, students are usually able to identify at least half of the letters of the alphabet [41, 65], but only a few students will be able to read words [65].

School leaders of primary schools in the Copenhagen area will be contacted by phone and invited to an initial non-committal meeting. All preschool teachers at the respective schools are encouraged to participate in this meeting. If the school leader and teachers agree to participate in the study, logistic planning will be done individually with all teachers to ensure that the final time schedule is in agreement with the respective teacher and class. All preschool children from schools enrolled in the study will be invited to participate in the project activities and assessments, however, children who do not speak any Danish or children with cognitive or physical disabilities hindering participation in the project activities will be excluded from the randomization and the final dataset and analyses. These children will be invited to attend the control activities. Further, only children whose parent(s) or legal guardian(s) provide signed written informed consent will complete the assessments. Children without consent will attend the control activities in the classroom but will not be included in the assessments and thus not the final dataset or analyses. All children will follow the interventions/control that they were initially allocated to.

